# Coding and randomization

All enrolled patients will have two codes, one is screening code, another is randomization code (study agent code). The screening code will be assigned to each potential patient during the screening. It consists of 6 digitals. The first 3 digitals stands for treatment center, the second 3 digitals is serial number assigned to subjects in terms of the screening sequence by each center.

The randomization code will be generated by an independent biostatistician who will not be involved in this study, using SAS program (SAS 9.0). Randomization will occur separately at each study center. Block randomization method will be applied in blocks of six. The block size and seed number will be sealed with the randomization list. The randomization code will be masked with 3 digitals serial number from 001 to 240. Each study agent vial will be labeled with a 3-digital number. The labeling of study agent will be processed by the personnel who will not be involved in this study according to the randomization list under the supervision of SFDA at Beijing Vaccine Institute. A randomization list will be kept at SFDA.

After screening, the eligible patient will be given a study agent in terms of the sequence of recruitment.

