**STUDY SYNOPSIS**

| Protocol No. | TG0508YIC |
| --- | --- |
| Title | Efficacy, safety of therapeutic hepatitis B vaccine (YIC) among chronic hepatitis B patients: a multi-center, randomized, double-blinded, controlled phase IIB clinical trial |
| Version | 2nd version, Oct 24, 2005 |
| SPONSOR | Beijing Vaccine Institute, and Shanghai Medical College, Fudan University |
| Phase | Phase IIB |
| Study population | Chronic hepatitis B patients |
| Objective | - To study the tolerance and efficacy of YIC among chronic hepatitis B patients through the comparison between 30 μg, 60 μg YIC and placebo groups. - To study the optimal regimen |
| Study design | Double-blinded, randomized, placebo-controlled trial with basic treatment. Subjects will be assigned to 30 μg, 60 μg YIC and placebo group equally. |
| Sample size | 240 patients |
| Number of study center | 12 |
| Duration | 44 weeks (0- 20 weeks treatment plus 24 weeks follow-up) |
| Selection Criteria | Inclusion criteria:   1. Patients with chronic hepatitis B aged 18 to 65 years; 2. Patients with > 6 months HBsAg positive prior to study; 3. HBeAg positive, HBeAb negative, and HBV DNA  1105 copies/ml; 4. Patients with ALT abnormal (2-fold higher but 10-fold less than cutoff at baseline.)   Exclusion criteria:   1. Co-infection with hepatitis A, C, D and E virus, or HIV; 2. Taking antiviral, hepatotoxic or immunosuppressive drugs or products within the preceding 6 months; 3. Other causes of liver disease; 4. Serious medical or psychiatric illness; 5. Hepatic cirrhosis or AFP>100 ng/ml; 6. Abnormal serum creatinine, thrombocyte count, 7. Hematoglobin or serum total bilirubin abnormal; 8. And pregnancy |
| Study agent | Vaccine:：therapeutic hepatitis B vaccine, 60 μg per ampoule.  Placebo：0.1% alum, 1 mL per ampoule |
| Study arm | Three arms, 80 cases for each.  Vaccine groups: 30 μg YIC and 60 μg YIC  Control group: placebo |
| Endpoints | The virologic response was assessed four weeks after the end of treatment (week 24) and at the end of follow-up (week 44). HBeAg seroconversion was defined by the loss of HBeAg and the presence of anti-HBe antibody. Suppression of HBV DNA was defined as > 2 log10 decrease of viral load.   - The primary endpoint was defined as loss of HBeAg, or presence of anti-HBe antibody or suppression of HBV DNA. - The secondary endpoint was designated as both HBeAg seroconversion and suppression of HBV DNA. |

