# Statistical Methods

All data will be double entered into custom-made data entry programs. The data management programs include range and consistency checks. An SAS program (SAS Institute Inc., Cary, NC, USA ) will be applied for statistical analysis.

- 1. Safety

The safety analysis will be performed based on the safety set (SS). It will include patients who received at least one injection, and completed at least one interview of safety evaluation after injection.

Three-wise comparison employed the chi square test, or Fisher’s exact test when data were sparse, for dichotomous outcomes will be performed to test the difference of occurrence of adverse events among placebo, 30 μg YIC and 60 μg YIC groups. A p-value < 0.05 (two-tailed) will be considered statistically significant.

- 1. Efficacy

The efficacy analysis will be conducted based on both full analysis and per-protocol sets. For full analysis set (FAS), it will include patients who were randomized, received at least one injection, and completed at least one interview of efficacy evaluation after injection. The intent-to-treat principle will be applied for the dataset. For per protocol set (PPS), it will include patients who met following three conditions：

1. Baseline information are available；
2. Complete full course of treatment and follow-up without protocol violation；
3. With good compliance (between 80% and 120%）.

For those important indicators, the missing data will be estimated using the most previous observation (LOCF, last observation carry forwards).

The primary efficacy hypotheses will be tested for response rate of primary endpoint in 30 μg YIC or/and 60 μg YIC groups > that in placebo group (2-tailed). The Chi square test, or Fisher’s exact test when data were sparse, will be employed. A p-value, point estimate, as well as confidence interval will be calculated.

The secondary efficacy outcomes will be summarized in a similar fashion.

Repeated measures analysis will be performed using a generalized estimating equations (GEEs) method to adjust the dependence among repeated observations made on the same patient while testing the group and time effects. A p-value < 0.05 (two-tailed) will be considered statistically significant.

- 1. Sample size

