Appendix 1. List of abbreviations

| AE | Adverse event |
| --- | --- |
| AFP | Alpha fetoprotein |
| ALB | Albumin BCG |
| ALT | Alanine aminotransferase |
| Anti-HBc | Antibody to Hepatitis B Core Antigen |
| Anti-HBe | Antibody to Hepatitis Be Antigen |
| Anti-HBs | Antibody to Hepatitis B Surface Antigen |
| ANOVA | Analysis of variance |
| AST | Aspartate aminotransferase |
| BUN | Blood urea nitrogen |
| CMH | Cochran-Mantel-Haenszel |
| Cr | Creatinine |
| CRF | Case report form |
| CTL | Cytotoxic T lymphocytes |
| DBIL | Direct Bilirubin |
| DRQ | Data Ramp query |
| ECG | Electrocardiogram |
| GCP | Good Clinical Practice |
| HAV | Hepatitis A Virus |
| HBIG | Hepatitis B immunoglobulin |
| HBsAg | Hepatitis B Surface Antigen |
| HBV DNA | Hepatitis B virus DNA |
| HCG | Human chorionic gonadotropin |
| HCV | Hepatitis C virus |
| HDL | High density lipoprotein |
| HDV | Hepatitis D virus |
| HEV | Hepatitis E virus |
| HIV | Human immunodeficiency virus |
| IC | Immune Complex |
| ICF | Informed consent forms |
| ICH | International Conference on Harmonization |
| IEC | Independent Ethics Committee |
| IRB | Institutional Review Board |
| ITT | Intent to treat |
| LDL | Low density lipoprotein |
| LOCF | Last Observation Carry Forward |
| pH | Hydrogen ion concentration |
| PP | “Per-protocol” population |
| PT | Prothrombin Time |
| PTA | Plasma thromboblastin antecedent |
| SAE | Serious adverse event |
| SFDA | China’s State Food and Drug Administration |
| TP | Total Protein |
| TBIL | Total Bilirubin |
| YMDD | tyrosine-methionine-aspartate-aspartate |

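### Randomisation is stratified by centre, but the primary test fixed in the protocol carries no centre term; the cost is a somewhat conservative test and, at the planned rates, little power

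*Protocol*

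**What the plan says.** Protocol section 7 (Coding and randomization) states: "Randomization will occur separately at each study center". It adds: "Block randomization method will be applied in blocks of six". The Synopsis gives 12 centres and 240 patients, 80 per arm, so 240/12 = 20 patients per centre on average, or 6 to 7 per arm per centre. Centre is therefore a stratification factor by design.

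Section 6.2 (Efficacy) sets the primary comparison of response rates as two-tailed ("YIC groups > that in placebo group (2-tailed") and names the method: "The Chi square test, or Fisher’s exact test when data were sparse, will be employed". It promises a p-value, point estimate and confidence interval, and treats the secondary outcomes in the same way. No centre factor is mentioned. The GEE analysis is described as adjusting for within-patient dependence "while testing the group and time effects". The term "Cochran-Mantel-Haenszel" appears in Appendix 1 (List of abbreviations), but the protocol text assigns it to no analysis.

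**The concern.** Blocking within centre makes the arms nearly equal in size in every centre, so differences between centres largely cancel out of the arm comparison. An unstratified test does not take this into account: its variance still includes the between-centre variation that the design has removed. The standard error is then too large on average, the test rejects a true null less often than 5%, and the confidence interval is wider than it need be.

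Two things are at stake. One is some power, mainly for 30 µg against placebo, the tighter of the two planned contrasts. The other is order: if the team wants a centre-adjusted result later, choosing it after unblinding would look post hoc, because section 6.2 has already named a different test.

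**Working it through.** **Inputs from the protocol.** 12 centres, 240 patients, 1:1:1 (Synopsis; section 4.3.3). Separate randomisation by centre, blocks of six (section 7). Response 20% vs 3% for 30 µg and 35% vs 3% for 60 µg, 80% power, 0.05 level, 20% dropout, 78 per arm (section 6.3).

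**Assumption.** Centre effects are normal on the logit scale with SD 0, 0.5, 1.0 or 1.5. The documents give no value.

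**The plan's own figure.** With unpooled variance and a two-sided level of 0.05/2 for the two contrasts:

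n = (2.241 + 0.842)² × (0.20×0.80 + 0.03×0.97) / (0.20 − 0.03)² = 62.19; 62.19/0.8 = 77.7, so 78 per arm.

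The protocol does not state that this was the method, but the figure reproduces. At 62 evaluable per arm, Fisher's exact test at 0.05 has 81.9% power. The calculation contains no centre term.

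**Why the unstratified test is conservative.** With p_c the response rate in centre c and p̄ the overall rate,

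p̄(1 − p̄) = average of p_c(1 − p_c) + between-centre variance of p_c.

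Chi-square uses the left side. CMH uses, in effect, only the first term on the right. With arms balanced within centres, that first term is the variance that matters. The gap is zero when centres do not differ and grows with the SD.

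**Simulation.** Each centre has 20 patients: three full blocks of six and two patients from a fourth. Dropout is 20% at random. There were 40,000 trials per setting, with tests two-sided at 0.05 (Pearson chi-square against CMH stratified by centre). The simulation standard error is about √(0.05×0.95/40,000) = 0.1 point for type I error and at most √(0.25/40,000) = 0.25 point for power.

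| Setting, 20% dropout (chi-square / CMH, %) | SD 0 | SD 0.5 | SD 1.0 | SD 1.5 |
|---|---|---|---|---|
| Type I error, 20% in both arms | 5.2 / 5.1 | 4.8 / 4.9 | 4.2 / 5.1 | 3.2 / 4.9 |
| Type I error, 3% in both arms | 3.4 / 3.4 | 3.3 / 3.3 | 3.0 / 3.2 | 2.5 / 3.1 |
| Power, 20% vs 3% (planned) | 89.8 / 88.8 | 89.8 / 89.3 | 89.8 / 90.1 | 89.4 / 91.3 |
| Power, 35% vs 3% (planned) | about 99.9 for both | about 99.9 for both | about 99.9 for both | about 99.9 for both |
| Power, 20% vs 8.3% (assumed) | 47.9 / 46.6 | 48.4 / 48.4 | 48.9 / 51.8 | 48.6 / 55.4 |

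At 20% vs 3% the change from using CMH is therefore −1.0, −0.5, +0.3 and +1.9 points. At 20% vs 8.3% it is −1.3, 0, +2.9 and +6.8 points.

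Without dropout, chi-square type I error at 20% response is 3.9% (SD 1.0) and 2.8% (SD 1.5), against 4.7% and 4.8% for CMH. Power at 20% vs 3% then moves from 95.6 / 95.4% (SD 0) to 95.1 / 96.2% (SD 1.5). Repeat runs agree with all of these to within about one point.

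**Source of the 8.3%.** Section 2.1 reports one placebo patient with HBV DNA suppression among 36 patients in three groups; 1/12 = 8.3% if the groups were equal. The group sizes are an assumption, the figure rests on one patient, and suppression there meant a level below 1.0×10⁵ copies/mL rather than the present fall of more than 2 log10. The row is a what-if and not an estimate.

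**The case against.** The strongest reply is that nothing is broken. Balance of the arms within centres is kept whatever test is used. The unstratified test does not inflate type I error; its error is on the safe side. At the protocol's own rates only 80 × 0.03 = 2.4 placebo responders are expected, 0.2 per centre, so stratification has little to gain. If centres do not differ, CMH loses about 1 point. All of this stands, and it is why the point is minor.

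A reader might infer that the stratification is wasted, or that the trial is underpowered because centre is left out. The documents support neither. The balance remains, and power for 20% vs 3% is about 89 to 91% in these simulations with either test.

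A reader might also take the CMH entry in the abbreviation list as a sign that a stratified analysis was planned and dropped. It shows little: the list also holds ANOVA, HDL and LDL, which the protocol text does not use.

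Nor does the wording on the GEE show that its model contains only group and time. Covariates in a supporting model are commonly left to the statistical analysis plan, so no criticism of the GEE is made here.

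It could be said that the statistical analysis plan, not among the documents reviewed, may adjust for centre. But section 6.2 names the primary test outright; a plan that replaced it with a stratified test would depart from the protocol. The Fisher alternative does not help, as it is unstratified too.

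Finally, the size of the centre effect is unknown. Section 4.4.2 has each centre's laboratory run the screening HBV DNA and uses screening results as baseline, with repeats at the reference laboratory. If local values served as baseline, laboratory differences could enter the response. That makes a centre effect plausible but does not measure it.

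**Conclusion.** The mismatch is real and stated in the protocol itself: randomisation is by centre, and the primary test ignores centre. The consequence is conservatism and not invalidity. At 20% response in both arms the chi-square type I error falls to about 4% at SD 1.0 and about 3% at SD 1.5, against about 5% for CMH.

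At the planned 20% vs 3% with dropout, CMH changes power by about −1 to +2 points; 35% vs 3% does not move. Only with a higher placebo rate and large centre differences does the gain become material: about +3 points at SD 1.0 and +7 at SD 1.5 for an assumed 8.3% vs 20%.

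These figures rest on an assumed between-centre SD, equal centres of 20 and dropout at random. This is a minor point, and no sample size changes.

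**What to change.** In section 6.2, replace the sentence ending "exact test when data were sparse, will be employed" by one that makes the primary test of each dose against placebo a CMH test stratified by centre. Report it with a Mantel-Haenszel risk difference and 95% CI. Keep the chi-square or Fisher test as a sensitivity analysis. If centre is to stay out of the primary test, the protocol should give the reason.

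The cost is one amended sentence and one option in the SAS procedure, settled before unblinding. The statistical downside is about 1 point of power if centres turn out not to differ.

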# Packaging and labeling

- 1. Packaging

Study agent vial will be packaged in paper box. One box will contain one vial. Every 6 boxes will be collected in one package.

- 1. Labeling

Each study agent vial will be coded with a 3-digital randomization number, which is between 001 and 240. Besides, injection date, dosage, and lot number will be printed with randomization code. Additional vaccination precautions will be printed on the package label.

# Handling and distribution of study agent

CRO (TigerMed Ltd.) will provide and update the administration record form for each study center. Each enrolled patient will have a unique allocation number. The administration record form will record status of dose received and returned, and injection date.

Investigational clinical supplies (including study agents and basic drugs) must be received by a designated person at the study center, handled and stored safely and properly, and kept in a secured location to which only the investigator and designated assistants have access. Clinical supplies are to be administrated only in accordance with the protocol. The investigator is responsible for keeping accurate records of the clinical supplies received from the CRO, the amount administrated to the patients, and the amount remaining at the end of each injection. All investigational clinical supplies-related records must be provided to monitor for inspection at each schedule and unscheduled monitoring visit. Used (empty ampoule and package) and unused study agent and basic drug should be returned to SPONSOR via CRO at the end of study.

1. ETHICAL CONSIDERATIONS
   1. Protocol Review

Before initiation of the trial, the working protocol requires clearance by the Ethic Committee and Institutional Review Board (IRB) in Beijing Ditan Hospital, which is the principle investigation institute.

According to the international standard guidelines on IRB, an annual review will take place to evaluate if the research has been conducted according to the protocol which was approved by initial review. Investigators will submit a progress report, which includes: report of adverse events occurred, subject recruitment status etc.

- 1. Ethical Guidelines

The principles that govern biomedical research involving human subjects are of application to this project. The Declaration of Helsinki (appendix 2) and the International Conference on Harmonization’s Good Clinical Practice Guidelines (ICH-GCP ) (appendix 3) will be followed, aiming to provide assurance that the rights, integrity, and confidentiality of trial subjects are protected and that results reported are credible and accurate.

- 1. Informed Consent

Consents will be sought during the screening stage. All efforts will be put in place to so that consent obtention is: informed, given voluntarily and given by a competent person. Inform consent procedures will follow the WHO/TDR Guidelines.

- 1. Confidentiality

Participant confidentiality in publications, reports and clinical or biological specimens collected during the conduct of the trial and following completion of the trial, will be ensured. Clinical or biological specimens will have an ID number or laboratory number only. The list linking names of the participants to the ID or laboratory number will be kept separately. Access to both electronic and hard copy data will be restricted to authorized senior study personnel only.

- 1. Potential Risks and Risk Minimization

### Vaccination

The most common adverse event in phase IIa trial was local reaction at injection site, followed by arthralgia, and erythra. Almost all adverse events were mild. Participant who received YIC might appear temporary ALT elevation, which could be well treated by medication. Serious adverse event was not observed. Adverse events, if deemed related to the vaccination process will be treated at the treatment center without charge.

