### Discontinuation/Withdrawal

Any patient who had signed a consent form, and meet the following criteria will be defined as premature withdrawal.

1. Patients who request to quit themselves;
2. Patients who violate the study protocol;
3. Patients who become pregnancy;
4. Patients who are unblinded due to SAE;
5. Patientsduring the treatment period who developed the following symptoms
   - - - Hepatic cirrhosis
       - Hepatic failure
       - And hepatoma.

If the withdrawal occurs due to the adverse events or abnormal laboratory tests, details should be recorded in the CRFs.

- 1. Laboratory assay

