### Measures taken after abnormal laboratory tests

When unexplainable abnormal laboratory test appears, the test must be repeated immediately , the patients should be followed-up constantly till either the abnormal test has resolved, or could be explained from investigator’s point of view. The definitive explanation should be recorded in the CRFs.

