### Treatment and follow-up of adverse events

Any adverse event must be treated with acceptable method. Investigators must report and discuss with SPONSOR when a method repelling with study agent has to be implemented, since this activity will cause premature withdrawal. All adverse events should be followed-up until the event has: resolved or subsided or stabilized or disappeared or the event is otherwise explained.

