### Important noticeable event

Important noticeable events is defined as any event which must be solved and recorded, such as treatment stopping, dose reducing, concomitant medication and withdrawal.

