### Secondary endpoint

The secondary endpoint was designated as both HBeAg seroconversion and suppression of HBV DNA.

- 1. Basic treatment

Considering the ethical issue, each patient who participates in this trial will be given basic treatment besides of study agents throughout 44-week study period as following:

- 1. Silymarin, 50 mg/tablets, 3 tablets per time, tid；
  2. Hu Gan Tablet, 0.36g per tablet, 4 tablets per time, tid.
  3. Concomitant medication

Concomitant medication is defined as: any vaccine, any other medication relevant to the protocol and administrated during the period starting from prior to treatment until the end of follow-up.

At each study center, the investigator should question the patient about any medication taken between two injections. All concomitant medication must be recorded in the CRFs with the trade name, generic name, indication, dose, route of administration, start and end dates of treatment.

The flowing drugs, treatments and behaviours are not allowed:

- 1. Any immunosuppressive or immunostimulant therapy, anti-viral therapy, drugs that have effects on decreasing the level of ALT, androgenic drugs, steroids, contraceptive drugs;
  2. Any investigational or non-registered anti-HBV drug, herbs or other patient self-chozen therapies
  3. Usage of acetaminophen more than 4 g per day;
  4. Intake of spirits more than 20 g per day;

1. Data management

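### Treating an ALT rise can end in withdrawal, and no virology serum is provided for after withdrawal, so avoidable efficacy data may be replaced by LOCF

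*Protocol*

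**What the plan says.** - **Risk (10.5.1 Vaccination).** "Participant who received YIC might appear temporary ALT elevation, which could be well treated by medication". No drug is named. Section 2.1 reports temporary ALT rises in some phase IIa participants, with recovery at follow-up.
- **Prohibition (4.8 Concomitant medication).** The list of what is not allowed includes "drugs that have effects on decreasing the level of ALT". It makes no exception for treating an adverse event.
- **Adverse-event treatment (4.5.7).** Every adverse event must be treated. The investigator consults the sponsor when "a method repelling with study agent has to be implemented, since this activity will cause premature withdrawal".
- **Withdrawal (4.3.8).** The criteria for premature withdrawal include "Patients who violate the study protocol". The data duty is: "If the withdrawal occurs due to the adverse events or abnormal laboratory tests, details should be recorded in the CRFs". Virology is not mentioned.
- **Abnormal tests (4.5.6).** When an abnormal result is unexplained, "the patients should be followed-up constantly till either the abnormal test has resolved" or can be explained. This concerns the abnormal test, not virology.
- **Serum (4.3.2 to 4.3.6, Appendix 2).** Virology serum is taken at screening and at weeks 12, 24, 36 and 44. The flow chart has no early-withdrawal visit.
- **Analysis (6.2).** For the full analysis set, "The intent-to-treat principle will be applied for the dataset". Entry requires at least one efficacy evaluation after an injection. Missing important indicators are filled by LOCF.

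**The concern.** Efficacy rests on HBV DNA, HBeAg and anti-HBe (4.6). Treating an ALT rise is no reason in itself to stop measuring them. Yet the rules, read together, let an investigator withdraw a patient for receiving an ALT-lowering drug, and nothing tells the site to keep drawing serum.

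Every patient enters HBeAg positive and anti-HBe negative (4.2.1). LOCF therefore credits only a response already present at the last sample and misses any that comes later. Section 2.1 itself says that responses to immunotherapy should be assessed some time after the last injection. A week 12 value is taken at the visit of the fourth of six injections.

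At stake are the 30 µg comparison with placebo and the choice between doses, which is a stated objective. This cannot be left to a statistical analysis plan, because an analyst cannot recover serum that was never drawn.

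**Working it through.** **1. What would be carried forward.** Safety bloods fall at eight post-baseline visits: weeks 4, 8, 12, 16, 20, 24, 36 and 44 (4.4.3). Assume that serum sampling stops at withdrawal. This is an inference, since the text is silent.

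| ALT rise found and patient withdrawn at | Last virology sample | Used for weeks 24 and 44 |
|---|---|---|
| Week 4 or 8 (2 of 8 checks) | Screening | Baseline carried forward, or patient leaves the full analysis set |
| Week 12, 16 or 20 (3 of 8) | Week 12 | Week 12 value, 12 weeks before week 24 and 32 weeks before week 44 |
| Week 24 | Week 24 | Week 24 observed, then carried to week 44 |
| Week 36 | Week 36 | Week 24 observed; week 36 carried to week 44 |

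**2. The plan's own figure.** Section 6.3 gives 78 per arm, 80% power, the 0.05 level and 20% dropout. The demanding comparison is 20% (30 µg) versus 3%. With 78 × 0.8 ≈ 62 evaluable per arm, Fisher's exact test has power 81.9% and the pooled normal formula 85.2%. The sample size is not in dispute.

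**3. Responses that would have to be missed.** With 80 per arm, the planned responders are 0.20 × 80 = 16 (30 µg), 0.35 × 80 = 28 (60 µg) and 0.03 × 80 = 2.4, so 2 or 3 (placebo). One missed response lowers an arm by 1/80 = 1.25 points. Chi-square, no continuity correction:

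- Placebo 2/80: 16/80 gives p = 0.0005; 9/80 gives 0.029; 8/80 gives 0.05004. Significance is lost after 16 − 8 = 8 missed responses (30 µg) or 28 − 8 = 20 (60 µg).
- Placebo 3/80: 16/80 gives p = 0.0015; 10/80 gives 0.043; 9/80 gives 0.072. Significance is lost after 16 − 9 = 7 (30 µg) or 28 − 9 = 19 (60 µg).

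**4. Power over an assumed range.** The protocol gives no rate of ALT treatment or withdrawal by arm. Let f be the share of an arm treated and withdrawn (assumed 0 to 20%, within the dropout allowance). Let r be the ratio of response probability in treated to untreated patients. Assume that none has responded by the last sample, that all stay in the full analysis set (80 per arm), and that there are no other dropouts. For true rate p:

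observed rate = p(1 − f) / (f·r + 1 − f)

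Example: p = 0.20, f = 0.20, r = 2 gives 0.16/1.20 = 0.133. Placebo is 0.03 if only the vaccine arm loses data, or 0.03(1 − f) if all arms do. Power is from the pooled-variance two-proportion formula, two-sided 0.05.

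| Arm | f | r | Observed rate | Power, vaccine arm only | Power, all arms |
|---|---|---|---|---|---|
| 30 µg | 0 | – | 20.0% | 92.8% | 92.8% |
| 30 µg | 10% | 1 | 18.0% | 87.9% | 89.6% |
| 30 µg | 20% | 1 | 16.0% | 80.7% | 85.2% |
| 30 µg | 10% | 2 | 16.4% | 82.2% | 84.4% |
| 30 µg | 20% | 2 | 13.3% | 66.8% | 73.3% |
| 60 µg | 20% | 2 | 23.3% | 97.3% | 98.2% |

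**5. If early withdrawals leave the full analysis set.** Suppose 2/5 of the 20% are withdrawn before week 12 (assumed). The 30 µg arm then has 80 × (1 − 0.08) = 73.6 patients and a rate of 0.20 × 0.8 × 80 / 73.6 = 17.4%. With r = 1 and placebo at 3% of 80, power is 84.8%, against 80.7% when all are carried forward.

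**The case against.** The strongest reply is that the chain is never shown to start. Section 10.5.1 names no drug, and every patient already takes Silymarin and Hu Gan, which section 2.1 describes as improving liver function. If that is the medication meant, nothing follows. This stands, and it is why the size may be zero.

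The link to withdrawal is also loose. Section 4.5.7 speaks of a method in conflict with the study agent and does not refer to the 4.8 list; an ALT-lowering drug need not conflict with a vaccine. Section 4.3.8 names cirrhosis, hepatic failure and hepatoma as hepatic reasons for withdrawal, not an ALT rise. Section 4.5.11 lists events "such as treatment stopping, dose reducing, concomitant medication and withdrawal" as separate items. And treatment that 4.5.7 itself orders is not obviously a protocol violation. All of this shows that withdrawal is possible rather than certain. It does not supply a rule that keeps the patient in follow-up.

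Some wording leans towards continued sampling: safety bloods for all enrolled patients to week 44 (4.4.3), virology on samples from all patients (synopsis), and the intent-to-treat statement. None of it says that serum is drawn after withdrawal.

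A reader might infer that the protocol contradicts itself by promising a treatment that it forbids. It does not: 4.5.7 gives a workable route (treat, consult, withdraw if the treatment conflicts), and the permitted basic treatment may be what is meant. Nor is the ban itself at fault. Laboratory testing is a safety endpoint in the synopsis, and keeping drugs that mask ALT out of the trial is sensible.

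**Conclusion.** The point holds as a minor gap in trial conduct. The prohibition has no adverse-event exception, withdrawal is a possible consequence, no virology serum is provided for afterwards, and LOCF fills what is missing in a set described as intention-to-treat.

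The size is unknown and possibly zero. Under the assumptions above, losing up to 20% of the vaccine arm leaves 30 µg power at 81% or more if treated patients respond like the others. It falls below the planned 80% only when, in addition, treated patients are twice as likely to respond (67% to 73%). Power for 60 µg stays at or above 97%. Where early withdrawals leave the full analysis set, the loss is somewhat smaller.

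A reader might infer a risk of a false claim of efficacy. The documents do not support that: patients enter without the serological response and LOCF misses later responses, so the bias probably runs against the vaccine. Excluding treated patients from the per-protocol set is normal and is not criticised. Confidence is medium, because the drug is unnamed and the end of sampling is inferred from silence.

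**What to change.** State in 4.8, 4.3.8 and 4.5.7 that medication given for an ALT-elevation adverse event is recorded as a deviation and may exclude the patient from the per-protocol set, but does not end follow-up. Collect the scheduled virology serum at weeks 12, 24, 36 and 44 regardless, and use these observed values in place of LOCF in the full analysis set. If the drug has antiviral activity, add a sensitivity analysis that counts the patient as a non-responder.

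Naming the medication in 10.5.1 and tabulating its use by arm would help but are optional.

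The cost is one amendment paragraph and, in the antiviral case, one extra analysis. The visits and samples are already scheduled, and concomitant medication and withdrawal are already recorded (4.8, 4.5.11). The downside is that virology measured after such a drug is somewhat harder to interpret.
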